**1. Introduction**

Typhoid Fever (TF) is a disease caused by the bacterium *Salmonella enterica* sv Typhi, which is contracted via faeco-oral transmission1. An inoculum as small as 100,000 organisms causes infection in more than 50% of healthy volunteers2. Humans are the only natural host and reservoir, and are infected through ingestion of faecally contaminated food or water. S. typhi may also be found in urine and vomitus of cases, and shellfish grown in sewage-contaminated water are potential vehicles, as are vegetables. Flies can mechanically transfer the organism to food, where the bacteria then multiply to achieve an infective dose. The highest incidence occurs where water supplies serving a large population are faecally contaminated. The incubation period is usually 8–14 days, but may range from 3 days up to 2 months. Some 2–5% of infected people become chronic carriers, who harbor *Salmonella* Typhi in the gall bladder. Chronic carriers are greatly involved in the spread of the disease3,4.

Clinical diagnosis of TF is challenging. In the absence of laboratory confirmation, any case of fever of at least 38 °C for 3 or more days is considered suspect if the epidemiological context is suggestive. Depending on the clinical setting and quality of available medical care, some 5– 10% of typhoid patients may develop serious complications, the most frequent being intestinal haemorrhage or peritonitis due to intestinal perforation.

An outbreak of TF has been recorded in Kikwit, Bandundu Province, in the Democratic Republic of Congo (DRC) in 2006 and 2011. Kikwit is the largest city of [Bandundu Province](http://en.wikipedia.org/wiki/Bandundu_(province)), lying on the [Kwilu River](http://en.wikipedia.org/wiki/Kwilu_River) in the southwestern part of the [Democratic Republic of Congo](http://en.wikipedia.org/wiki/Democratic_Republic_of_Congo). The population is approximately 350,000. Since the 2006 reported outbreak, TF has been endemic in Kikwit, with limited cases reported in 2009, 2010 and the 3 first trimestres of 2011.

Figure 1 shows the epidemic curve for Typhoid Fever cases from January 1, 2009 to December 31, 2011.

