In Kikwit, the environment is mountainous with in the extreme north the river Kwilu. Between the different mountains exist small rivers and springs. Availability of potable water is challenging, especially in “Kikwit ville basse”, the lower lying part of Kikwit town. Piped water is too expensive for most of the population and its quality is compromised by inappropriate chlorination, and a leaking distribution network that allows aspiration of surface water when the pumps stop turning and the water pressure drops within the network. The price of the water also compromises its accessibility considerably. As a coping mechanism, the population uses open, unprotected springs to collect drinking water. Up to four or five springs can be identified per “aire de sante” and they well up at the bottom of the slopes in this mountainous environment. These sources are often situated close to small tributary rivers of the main river Kwilu. Only about 50 % of people in Kikwit own a latrine and wild defecation is rampant, also uphill of springs, leading to a high-risk environment for TF transmission. The central market of Kikwit also has an important potential to maintain TF transmission, with an absence of water and hand washing points on the market itself. Only one individual is responsible for cleanness in the market and most goods are presented on the ground instead of on tables. No latrines are available on the market.

3.3. Study site:

MSF is supporting Kikwit Nord General Hospital in order to offer free and quality treatment to simple TF patients as well as to those suffering from complications or perforation. Simple cases are given outpatient care and antibiotics, while complicated cases are hospitalized and perforated cases receive surgical treatment. MSF also provides medicines to the hospital, gives training to the personnel of the hospital and health centers around the city, and ensures that an adequate case definition and treatment protocol are implemented. Community workers are raising awareness among the population about basic hygiene practices, in order to halt this serious epidemic of TF, the so-called "dirty-hands disease”. These interventions are part of an emergency response, despite the fact that the problem is systemic and has repeated itself each 5 years in Kikwit.

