## 3.5. Sample size

Two controls will be selected for each case. In order to identify an Odds Ratio of at least 1.5 with a power of 80% for risk factors present in 30% of the control population, a sample size of 320 cases and 640 controls was calculated.

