## 3.10. Chemical and biological water tests

## No major improvements have been made to the water distribution infrastructure since November 2011, and water quality testing can thus still be performed, as results are likely to reflect the conditions of 2011. Two tests will be used to evaluate the quality of water being consumed: a test to measure the free residual chlorine and a test to evaluate the presence of coliform bacteria. The chlorine test will be performed on water samples collected from the household water reservoir and when possible from the water source used by the household. This will be done using a spectrometer HANNA HI 701 Checker © HC² (HANNA ©Instruments, USA). The level of 0,2 mg/l will be considered as sufficient to consider the water as potable. The test of presence of coliforms will be done only on a water sample collected from the household water reservoir with the help of the test AquaCHROM TM (CHROMagar TM, France).

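### Section 3.10 fixes coliform presence as the only microbiological water exposure and names no faecal indicator, so the planned power for an odds ratio of 1.5 may not carry over to faecal contamination

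*Protocol*

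**What the plan says.** Section 3.10 lists two water tests. One measures free residual chlorine. The other is "a test to evaluate the presence of coliform bacteria", and it is restricted: "The test of presence of coliforms will be done only on a water sample collected from the household water reservoir". A commercial product is named, but the section does not say which organisms are read from it, whether a faecal indicator is separated from other coliforms, or whether anything beyond presence is recorded. Section 3.12 takes the water-quality variables from 3.10 and adds no other microbiological measure.

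The hazard described elsewhere is faecal. The Introduction states: "Humans are the only natural host and reservoir, and are infected through ingestion of faecally contaminated food or water". The setting in section 3.2 is described in the same terms: "Only about 50 % of people in Kikwit own a latrine and wild defecation is rampant, also uphill of springs".

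Section 3.5 plans the study "for risk factors present in 30% of the control population" and an odds ratio of at least 1.5 at 80% power; "a sample size of 320 cases and 640 controls was calculated". These figures are for risk factors in general. The protocol gives no expected prevalence for contaminated household water.

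**The concern.** The exposure of interest and the exposure measured are not the same. As a matter of general microbiology, which the protocol does not discuss, coliforms as a group include organisms from soil and vegetation as well as from faeces. Section 3.2 says that much of the population collects drinking water from open, unprotected springs. Such water, stored at home, could test positive without faecal contamination. A group-wide yes/no result would then count those homes as exposed.

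If this happens equally in cases and controls, it is non-differential misclassification of a binary exposure, and it biases the odds ratio towards 1. It also pushes positivity up in both groups, and a presence-only result cannot grade contamination once most homes are positive.

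Water is a leading hypothesis in the Introduction, and section 4.3 expects the results to help obtain funds for the water distribution network. A weak or null coliform association that reflected the choice of indicator would be unhelpful there.

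**Working it through.** **Inputs from the protocol (3.5):** odds ratio 1.5; exposure in controls p0 = 0.30; 320 cases and 640 controls; power 80%.

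**Assumed, because the protocol does not state them:** two-sided 5% test; sensitivity (Se) of coliform presence for faecal contamination = 1; specificity (Sp) 0.9 to 0.3; true faecal contamination in 30%, 50% or 70% of control homes; the same Se and Sp in cases and controls.

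**Step 1: reproduce the plan's sample size.**

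p1 = OR·p0 / (1 − p0 + OR·p0) = 0.45 / 1.15 = 0.391.

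With two controls per case, the weighted mean is p̄ = (0.391 + 2 × 0.30)/3 = 0.330, and

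n = [1.96·√(1.5·p̄(1 − p̄)) + 0.842·√(p1(1 − p1) + p0(1 − p0)/2)]² / (p1 − p0)² = 316 cases.

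This is close to the stated 320. A one-sided 5% test would give 249, so the two-sided assumption fits the plan.

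Power at 320/640 is Φ[(|p1 − p0| − 1.96·s0)/s1], where s0 = √(p̄(1 − p̄)(1/320 + 1/640)) = 0.0322 and s1 = √(p1(1 − p1)/320 + p0(1 − p0)/640) = 0.0327. The argument is (0.0913 − 1.96 × 0.0322)/0.0327 ≈ 0.86, so power is 80.5%.

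**Step 2: add false positives.**

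Observed positivity is q = p·Se + (1 − p)(1 − Sp), computed separately for cases and controls.

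Example with 30% prevalence and Sp = 0.7:
- controls: 0.30 + 0.70 × 0.30 = 0.510
- cases: 0.391 + 0.609 × 0.30 = 0.574
- observed OR: (0.574/0.426)/(0.510/0.490) = 1.29
- power from the formula in step 1: 46%

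**Step 3: the range (true OR 1.5, Se = 1).**

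| True prevalence, controls | Sp | Controls positive | Cases positive | Observed OR | Power |
|---|---|---|---|---|---|
| 30% | 1.0 | 0.300 | 0.391 | 1.50 | 80.5% |
| 30% | 0.9 | 0.370 | 0.452 | 1.41 | 69% |
| 30% | 0.8 | 0.440 | 0.513 | 1.34 | 57% |
| 30% | 0.7 | 0.510 | 0.574 | 1.29 | 46% |
| 30% | 0.5 | 0.650 | 0.696 | 1.23 | 29% |
| 30% | 0.3 | 0.790 | 0.817 | 1.19 | 16% |
| 50% | 1.0 | 0.500 | 0.600 | 1.50 | 84% |
| 50% | 0.8 | 0.600 | 0.680 | 1.42 | 68% |
| 50% | 0.5 | 0.750 | 0.800 | 1.33 | 41% |
| 70% | 1.0 | 0.700 | 0.778 | 1.50 | 73% |
| 70% | 0.9 | 0.730 | 0.800 | 1.48 | 67% |
| 70% | 0.7 | 0.790 | 0.844 | 1.44 | 52% |
| 70% | 0.5 | 0.850 | 0.889 | 1.41 | 37% |

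Lower sensitivity makes matters worse: at 30% prevalence with Se = 0.9 and Sp = 0.8, the OR is 1.30 and power 47%.

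The formulas treat the samples as unmatched. A matched calculation with no correlation of exposure within sets also gives 316 cases.

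**The case against.** The strongest objection is that the protocol does not say that coliforms as a group are what is recorded. It names a product and is silent on what that product separates. If the product already distinguishes E. coli, what remains is a failure to say that this result will be read and analysed. This stands, and it is why the point is conditional.

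A reader might also infer that a true odds ratio of 1.5 would show up as about 1.2 to 1.3 and usually be missed. The documents do not support that as a statement of fact. At 30% prevalence and full sensitivity it needs a specificity of roughly 0.35 to 0.7, and power stays above one half once specificity exceeds about 0.73. The 30% is itself a generic planning value. Section 3.2, with its account of open defecation, suggests that contamination may be more common. At 70% prevalence the odds ratio barely attenuates, and part of the shortfall from 80% comes from the high prevalence itself, since even a perfect reading has only 73% power. E. coli would share that part. A stronger effect could also survive: with a true OR of 2.0, 30% prevalence and specificity 0.7, power is 92%.

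Nor would a null coliform result by itself lead to the conclusion that water is not a risk factor. Section 3.9 lists the water tests as complementary, section 3.12 centres the study on questionnaire variables, and water source, storage, treatment and chlorine all bear on the same route.

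Finally, samples are taken between November 2012 and February 2013 for an outbreak in November and December 2011. Any change in household water over that year affects an E. coli reading too. The calculation above leaves this out, so it does not show how much power the fix would deliver in practice.

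These points limit the size of the claim. They do not remove the mismatch between the faecal hazard described and the indicator specified.

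**Conclusion.** The point holds in conditional form. Section 3.10 specifies one microbiological exposure, coliform presence, and no faecal indicator. If that is recorded as a group-wide yes/no result with specificity below 1 for faecal contamination, equal in cases and controls, the odds ratio for faecal contamination is biased towards 1. Power then falls below that of a perfect faecal reading in every scenario computed.

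The direction is firm under those conditions; the size is not. The loss runs from modest (at 70% prevalence and specificity 0.9, power is 67% instead of 73%) to severe (at 30% prevalence and specificity 0.3, 16% instead of 80.5%). The protocol gives neither the specificity nor the prevalence needed to choose between them. Because the water tests are one of several exposure groups, this is a worthwhile improvement to one exposure measure and does not threaten the study as a whole.

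**What to change.** In section 3.10, state that E. coli is read and recorded as present or absent, separately from other coliforms, on the same reservoir sample. State that E. coli is analysed as the faecal-contamination exposure and that any-coliform presence is kept as descriptive. Check the instructions of the named product first; only if that version does not separate E. coli, use a medium that does.

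The cost is a sentence or two in 3.10, one extra field on the water form and possibly a change of medium. No additional sample or visit is needed. If the result is not recorded when the test is read, it may not be recoverable later. The change does not correct misclassification from sampling about a year after the outbreak, so that limitation should still be acknowledged when the water results are interpreted.

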## 3.11. Main outcome measures

The main outcome measures in this study is TF incidence, both simple cases and cases with peritonitis and intestinal perforation.

## 3.12. Variables

For each respondent, all variables contained in the survey questionnaire will be collected. The study is centered on demographics and household composition, household water sourcing and storage, hygiene practices, and food/drink hygiene practices. The variables collected are listed in full in the questionnaire in Annex I. Additionally, variables pertaining to water quality will be collected per household (cf. §3.10.).

## 3.13. Data and statistical analysis

Questionnaire results will be encoded in full. Data will be processed and analysed (bivariate and multivariate analysis) using Epi-Info and STATA software packages. For all individual variables, results will be analyzed as three groups, respondents contracting simple, complicated or no TF during the 2011 outbreak.

4. Ethics issues:

The general medical and sanitation activities during the Kikwit Typhoid Fever outbreak response were part of the overall MSF emergency response and were in line with standard MSF conduct. General measures were in place to ensure confidentiality and support for all patients, as is standard MSF practice, and these measures will also be respected while conducting the survey. All care provided to the patients was free of charge, as standard for MSF. Data included in this analysis will not include patient identifiers. The nature and purpose of the survey will be explained to each household and verbal consent will be obtained from every individual prior to survey administration. Ethical approval will be sought from the Ethics Review Boards of MSF and the Ministry of Health of DRC in order to perform the analysis of the survey in full compliance with the ethical requirements within DRC and MSF.

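### The 80% power in section 3.5 is for all TF cases versus controls, but section 3.13 states only a three-group comparison, which does not carry that power

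*Protocol*

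**What the plan says.** Protocol section 3.5 (Sample size) takes 80% power and an odds ratio of 1.5 or larger as its basis; on these terms, "for risk factors present in 30% of the control population, a sample size of 320 cases and 640 controls was calculated". There are two controls per case. That is a single two-group contrast. Section 3.5 does not mention severity.

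Section 3.13 (Data and statistical analysis) announces bivariate and multivariate analysis and then fixes one comparison structure: "For all individual variables, results will be analyzed as three groups, respondents contracting simple, complicated or no TF during the 2011 outbreak". It names no test, reference group, significance level or adjustment for several comparisons. It does not mention a comparison of all cases with controls.

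Section 3.11 (Main outcome measures) covers both case types in one sentence: "The main outcome measures in this study is TF incidence, both simple cases and cases with peritonitis and intestinal perforation". Section 2 gives the aim as finding risk factors for TF transmission, without reference to severity. Section 1 reports the 2011 outbreak as 1438 cases, of which 1367 were simple and 71 had peritonitis and perforation. Section 3.6 draws cases at random from the line list and states no stratification by severity.

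**The concern.** The contrast that was sized and the comparison that is written down are not the same. A reader would attach the 80% in 3.5 to the analysis in 3.13, where it does not belong. Splitting the cases costs power in one of two ways. An overall three-group test spends a second degree of freedom. Separate comparisons leave one very small case group.

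Two things are at stake. A real risk factor with OR 1.5 could be missed more often than the protocol implies. And a null result for complicated cases could be read as evidence of no association, when the study had little chance of finding one. The pooled contrast answers the aim in section 2 and delivers the stated power, but 3.13 does not say that it will be made.

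**Working it through.** **Inputs**
- Section 3.5: exposure in controls p0 = 0.30, OR = 1.5, 320 cases, 640 controls.
- Section 1: 71 complicated among 1438 cases.
- Assumed, because the protocol does not state them: two-sided 5% level; OR 1.5 in both case types; unmatched normal approximation; the city-wide complicated share also holds for the sampled cases. The range for the last assumption runs from about 16 complicated cases up to all 71.

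**Exposure in cases**

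p1 = OR·p0 / (1 − p0 + OR·p0) = 0.45 / 1.15 = 0.3913, so the difference is d = 0.0913.

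**Reproducing the figure in 3.5**

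The two-proportion formula with pooled null variance and a 1:2 ratio gives 316 cases, against 320 stated. A one-sided 5% level would give 249, so the two-sided assumption fits.

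Power = Φ[(d − 1.96·SE0) / SE1], where SE0 uses the pooled proportion and SE1 the separate proportions. For 320 versus 640:
- pooled proportion = (320 × 0.3913 + 640 × 0.30) / 960 = 0.3304
- SE0 = 0.03220, SE1 = 0.03275
- (0.0913 − 1.96 × 0.03220) / 0.03275 = 0.861, so power = **80.5%**

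A 1:2 matched formula with zero within-set exposure correlation gives 80.6%. The stated size is therefore correct for the pooled contrast.

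**Expected split of the cases**

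71 / 1438 = 4.9%, and 320 × 0.0494 = 15.8. That is about 16 complicated and 304 simple cases.

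**Reading A: one overall test of the three groups (2 df)**

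Noncentrality λ = Σ n_i (p_i − P)² / [P(1 − P)], with P = 0.3304. With a common OR of 1.5:
- cases: 320 × (0.3913 − 0.3304)² = 1.186
- controls: 640 × (0.30 − 0.3304)² = 0.593
- λ = (1.186 + 0.593) / 0.2212 = 8.04

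Against the 5% critical value of 5.99 on 2 df, power = **72.0%**. Under a common OR this does not depend on how the 320 cases divide, since λ is the same for any split.

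If the OR differs in complicated cases (304 simple at OR 1.5, 16 complicated):

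| OR in complicated cases | Three-group test, 2 df | Pooled contrast |
|---|---|---|
| 1.0 | 70.9% | 76.6% |
| 1.5 | 72.0% | 80.5% |
| 2.0 | 77.0% | 83.3% |
| 3.0 | 87.1% | 86.8% |

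Of these values, only at 3.0 does the three-group test draw level with the pooled contrast.

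**Reading B: each case group against all 640 controls, two-sided 5% each**

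| Complicated cases sampled | Simple vs no TF | Complicated vs no TF |
|---|---|---|
| 16 | 79.2% (304 cases) | 13.4% |
| 71 | 73.7% (249 cases) | 35.9% |

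For the 13.4%: SE0 = 0.1162 and SE1 = 0.1233, so (0.0913 − 1.96 × 0.1162) / 0.1233 = −1.107. With 16 complicated cases, 80% power needs an OR of about 4; with 71 it needs about 2.

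**The case against.** The strongest reply is that 3.13 does not name a 2-df test. Section 3.5 speaks of identifying an odds ratio, which an overall chi-square does not provide. The more natural reading may be one odds ratio per case type against no TF, and then simple versus none keeps 79.2%, about one point below the pooled figure. This stands. A reader might infer that the study's power simply falls to about 72%, or that a true risk factor is missed 28% of the time. The protocol does not support that as a flat statement, because it holds only under Reading A with a common OR.

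It can also be said that the pooled contrast is implicit. The design is case-control, controls are selected without regard to severity, and the aim concerns TF as a whole. Which contrast is primary could be left to a statistical analysis plan. This has some force, but 3.13 is not silent. It states a comparison structure, and that structure differs from the one that was sized.

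Two smaller reservations also stand. The phrase about individual variables may mean respondent-level variables only, since section 3.8 distinguishes these from household-level information; household water and sanitation exposures might then fall outside the sentence. And the figure of 16 complicated cases applies a city-wide share to cases aged 10 or over in 7 health areas, so it is an assumption and is shown with a range.

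**Conclusion.** The mismatch holds. Section 3.5 states power for all cases versus controls, section 3.13 states a three-group comparison, and the stated 80% does not carry over to every comparison under either reading. An overall 2-df test has about 72%. Pairwise comparisons have about 79% for simple cases (74% if 71 are complicated) and about 13% for complicated cases (36% if 71). On the pairwise reading the loss for simple cases is small, and the clear shortfall is in the complicated group.

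These figures rest on the assumptions listed in the working. The unmatched approximation ignores any within-set exposure correlation, for which the protocol gives no value.

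It would be wrong to conclude that the sample size in 3.5 is in error. It reproduces for the contrast it describes, and 72% is not a corrected value for it.

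**What to change.** In section 3.13, state that the primary comparison for each risk factor is all TF cases (simple plus complicated) versus controls, with one odds ratio, as sized in 3.5. State that the simple / complicated / no TF breakdown is secondary and descriptive, and that the 80% power applies only to the pooled contrast. Leave the power in 3.5 unchanged.

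The cost is a sentence or two of text. It needs no new data, and the severity results are still reported. The one downside is that a factor acting only on severity becomes a secondary finding. With about 16 complicated cases expected, the study could not have supported a firm conclusion on such a factor unless the effect was very large.

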**3. Methods**

3.1. Study Design:

A observational case-control study with individual matching for age and sex.

3.2. Setting:

Kikwit is the largest city of [Bandundu Province](http://en.wikipedia.org/wiki/Bandundu_(province)), lying on the [Kwilu River](http://en.wikipedia.org/wiki/Kwilu_River) in the southwestern part of the [DRC](http://en.wikipedia.org/wiki/Democratic_Republic_of_Congo). The population is approximately 350,000. The situation in DRC is dramatic in terms of health provision, with a weak health system, extremely poor accessibility of the existing health system and regular emergency levels of mortality figures, even in stable districts. These negative indicators are the result of, amongst others, decades of civil war and unrest, poor infrastructure and challenging geographical features, and poor management of the existing resources.

The sanitary district of Kikwit lies about 500 kilometers east of the capital, Kinshasa. It has a supervisee of 330 km² and a population density of approximately 1282 habitants per km². It is composed of 2 “zones de santé”:

- ZS de Kikwit Nord (161,046 habitants), 18 “aires de santé”, comprising 2 communes: Lukolela et Nzinda.
- ZS de Kikwit Sud (176,300 habitants), 15 “aires de santé”, comprising 2 communes: Lukeni et Kazamba

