## 3.4. Study population

The study population consisted of TF cases randomly selected from the line list of cases who are living within 7 out of the 33 “aires de santé”, believed to be hotspots of TF transmission within Kikwit.

The case definition during the outbreak was provided jointly by the Ministry of Health and the World Health Organization. A **Suspected case** is any person with gradual onset of steadily increasing and then persistently high fever, malaise, headache, sore throat, cough, and, sometimes, abdominal pain and constipation or diarrhea. A **Confirmed case** is asuspected case confirmed by isolation of *Salmonella* Typhi from blood, bone marrow, duodenal fluid or stool. For the confirmation of TF, isolation of *Salmonella* Typhi is required. Blood culture is the mainstay of the diagnosis. In endemic areas, stool isolation alone is insufficient for diagnosis if the clinical picture is not complete.

Two controls of the same sex, age class (10 to 14, 15 to 19, 20 to 29, 30 to 39, 40 to 49 and more than 50) and “aire de santé” will be selected per case. Selection criteria for controls are not having been suspected of TF during the study period and having the possibility to present themselves at the health structure during the study period if required.

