## 3.6. Sampling procedure

A representative sample of cases will be selected by random sampling, using random numbers generated in MS Excel, from a line list of cases who are living within the 7 “aires de santé” believed to be hotspots of TF transmission within Kikwit. Controls will be selected in two phases.

In the first phase, a geo-referenced polygon around each of the the 7 “aires de sante” will be generated from images obtained from Google Earth. Then with the help of the software package R, a total of 1500 random points will be generated within this polygon and the geographic coordinates of each point will be registered. Again, with the help of Google Earth images, all the points not falling on the roof of a house will be eliminated. Finally, 640 houses will be selected at random from the remaining points and allocated to cases: the first and the second point will be allocated to case 1, the third and fourth to case 2, and so on. As such, each case of the study population will have 2 random points allocated that each correspond to a house within the polygon.

In the second phase, with the help of a GPS, the corresponding houses will be visited by field teams. Within the household, a control will be recruited, matching the corresponding case in sex and age, and without suspicion of TF during the study period. If within this household no one matches the case or no one corresponds to the control criteria, then the field team will survey the next occupied building to the right. A household is defined as a group of people sleeping in the house and sharing the meals regularly during the study period.

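### Controls are recruited in individually matched 1:2 sets, but the only stated comparison is between three respondent groups with no reference to the sets, and the main outcome is an incidence that the sample cannot estimate

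*Protocol*

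**What the plan says.** **Design.** Section 3.1 describes "A observational case-control study with individual matching for age and sex". Section 3.4 asks for "Two controls of the same sex, age class (10 to 14, 15 to 19, 20 to 29" and so on through the older classes, and then adds the aire de santé as a third matching factor. Section 3.6 links control houses to cases in sequence: "the first and the second point will be allocated to case 1, the third and fourth to case 2". In the field, "a control will be recruited, matching the corresponding case in sex and age, and without suspicion of TF during the study period". Aire is not named in that step.

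**Size.** Section 3.5 gives 320 cases and 640 controls "In order to identify an Odds Ratio of at least 1.5 with a power of 80" per cent, "for risk factors present in 30% of the control population".

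**Outcome.** Section 3.11: "The main outcome measures in this study is TF incidence", covering simple cases and those with peritonitis and perforation.

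**Analysis.** Section 3.13 names bivariate and multivariate analysis in Epi-Info and STATA, without naming a model, and gives one rule for every variable: "For all individual variables, results will be analyzed as three groups, respondents contracting simple, complicated or no TF during the 2011 outbreak".

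**Rates.** Section 3.9 takes the description of the epidemics from the Ministry of Health line list, and denominators for rates from the census bureau.

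**The concern.** Each control is chosen to resemble one particular case. The controls taken together therefore have the cases' distribution of matching factors, not that of the source population. The usual remedy is to compare within sets, or at least to adjust for the matching factors. Section 3.13 states a unit of comparison, and it is not the set: a single no-TF group carries no link to the case for which each control was recruited. If the factors are left out and exposure varies with them, the crude odds ratio is closer to 1 than the matched one. The study is sized for an odds ratio of 1.5 with almost no margin, so even modest attenuation costs power.

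The outcome in section 3.11 is a separate problem. With two controls taken per case, the proportion of respondents with TF is one third by construction. It says nothing about incidence.

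**Working it through.** **1. The protocol's own sample size.** Inputs from section 3.5: control exposure p0 = 0.30, OR = 1.5, power 80%, r = 2 controls per case. Alpha is not stated; 0.05 two-sided is assumed.

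- Exposure in cases: p1 = 1.5 × 0.30 / (1 + 0.30 × 0.5) = 0.3913.
- Mean exposure: p̄ = (0.3913 + 2 × 0.30) / 3 = 0.3304.
- Unmatched two-proportion formula: n = [1.960·√(1.5·p̄(1−p̄)) + 0.842·√(p1(1−p1) + p0(1−p0)/2)]² / (p1 − p0)² = 315.6, so 316 cases and 632 controls.

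This is close to 320 and 640, where power is 80.5%. The stated number is what an unmatched calculation gives, so section 3.5 makes no visible allowance for matching either. A matched 1:2 formula (Dupont) gives 316 cases at zero case-control correlation of exposure, 343 at 0.1 and 378 at 0.2. The protocol gives no correlation.

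**2. What ignoring the sets could do.** Assume matching on aire (section 3.4), seven aires with equal numbers of cases, control prevalences p_k equally spaced over a range, and a common true odds ratio.

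- Case prevalence in aire k: c_k = OR·p_k / (1 − p_k + OR·p_k).
- Crude odds ratio: [C/(1−C)] / [P/(1−P)], where C and P are the means of c_k and p_k.

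Example, 15%-45%, OR 1.5: p_k = 0.15, 0.20, 0.25, 0.30, 0.35, 0.40, 0.45, with mean P = 0.30. The c_k are 0.209, 0.273, 0.333, 0.391, 0.447, 0.500, 0.551, with mean C = 0.3864. Crude OR = (0.3864/0.6136) / (0.30/0.70) = 1.47.

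| Assumed spread over aires | P | C at OR 1.5 | Crude OR, true 1.5 | True 2.0 | True 3.0 |
|---|---|---|---|---|---|
| No variation | 0.300 | 0.391 | 1.50 | 2.00 | 3.00 |
| 20%-40% | 0.300 | 0.389 | 1.49 | 1.97 | 2.92 |
| 15%-45% | 0.300 | 0.386 | 1.47 | 1.93 | 2.82 |
| 5%-60% | 0.325 | 0.403 | 1.40 | 1.77 | 2.45 |

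A second route, with normally distributed set-level log-odds of exposure and control prevalence held at 30%, agrees. A true 1.5 appears as 1.50, 1.47, 1.40 and 1.34 at within-set exposure correlations of 0, 0.05, 0.16 and 0.27.

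Power of an unmatched comparison of 320 with 640 at 30% control exposure is 80.5% for an odds ratio of 1.50, about 76% for 1.47 and about 65% for 1.40.

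**3. Complicated cases.** The Introduction reports 71 of 1438 cases with peritonitis and perforation, or 4.9%. If cases are sampled in that proportion (an assumption), 320 × 71/1438 = 15.8, so about 16 are complicated and 304 simple. Of the 640 controls, 608 (2 × 304) would then have been recruited for simple cases. Power for an odds ratio of 1.5, with 16 complicated cases against all 640 controls, is about 13%.

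**4. Incidence.** The sample fixes 320 with TF and 640 without: 320/960 = 1/3 whatever the true attack rate. The odds ratio does not depend on that ratio, and it is the measure in section 3.5. Rates need the line list as numerator and the census as denominator (section 3.9).

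**The case against.** A reader might infer that the protocol prescribes pooling and an unconditional model. It does not say so. Section 3.13 names no model, and three outcome categories are compatible with keeping the sets: simple cases against their own controls, and complicated cases against theirs. Choice of model is also commonly left to a statistical analysis plan, which is not at hand. This stands, and it limits the point to what section 3.13 does state: a comparison unit for all variables that does not refer to the sets.

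A reader might also infer that odds ratios will certainly be attenuated, and most of all for water, latrine and market exposures. The document does not support this. Attenuation needs exposure to vary with the matching factors and those factors to be left out. The factors are coarse (6 age classes × 2 sexes = 12 strata, or 84 with seven aires), so a multivariable model containing them would largely remove the bias. Section 3.2 describes springs within each aire and poor water supply in the lower town, but gives no prevalence by aire. The mechanism computed above also requires matching on aire, which only section 3.4 states. If controls are recruited as sections 3.1 and 3.6 describe, those figures do not apply.

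Finally, incidence is not out of reach for the study as a whole, since section 3.9 provides a source for rates. It is out of reach for the case-control sample.

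**Conclusion.** The point holds in limited form. The recruitment sections build matched sets, and the one stated comparison does not carry them into the analysis. Followed literally, it gives odds ratios biased towards 1 for exposures associated with the matching factors. The size cannot be determined from the document. For a true 1.5 it runs from none to about 1.40 over the spreads tabulated, and the milder spreads lose only 0.01 to 0.03. All of these figures assume matching on aire, equal case numbers per aire and no adjustment.

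The outcome error needs no assumption: section 3.11 names a quantity that a fixed 1:2 sample cannot estimate and that differs from the measure on which section 3.5 is powered.

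The conflict over aire is part of the same problem, because it decides what a matched set is.

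**What to change.** - **Section 3.11:** name the matched odds ratio for TF as the main measure. Report incidence only descriptively, from line list and census.
- **Section 3.13:** specify conditional logistic regression on the matched sets for the bivariate and multivariable analyses, or a model adjusting for sex, age class and aire. Compare simple and complicated cases each with their own controls. Keep the three-group table as description, given the few complicated cases expected.
- **Sections 3.1, 3.4 and 3.6:** reconcile whether aire de santé is a matching factor, and make the allocation of houses to cases in 3.6 agree. The data set must carry the set identifier.

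The cost is wording. The planned data and the STATA package already named suffice for the analysis. Only the aire question could touch field procedure, if the allocation of houses has to respect it. Settling this before the data are analysed also removes a later choice between matched and unmatched results.
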